## Abstract

**Background:**

Preeclampsia and intrauterine fetal growth restriction (IUGR) are two of the most common causes of maternal and perinatal morbidity and mortality. Current methods of predicting those at most risk of these conditions remain relatively poor, and in clinical practice past obstetric history remains the most commonly used tool. Aspirin and, in women at risk of preeclampsia only, calcium have been demonstrated to have a modest effect on risk reduction. Several observational studies and randomised trials suggest that low molecular weight heparin (LMWH) therapy may confer some benefit.

**Methods/design:**

This is a multicentre open label randomised controlled trial to determine the effect of the LMWH, enoxaparin, on the prevention of recurrence of preeclampsia and/or IUGR in women at high risk due to their past obstetric history in addition to standard high risk care for all participants.

Inclusion criteria: A singleton pregnancy >6^+0^ and <16^+0^ weeks gestation with most recent prior pregnancy with duration >12 weeks having; (1) preeclampsia delivered <36^+0^ weeks, (2) Small for gestational age (SGA) infant <10^th^ customised birthweight centile delivered <36^+0^ weeks or, (3) SGA infant ≤3^rd^ customised birthweight centile delivered at any gestation. Randomisation is stratified for maternal thrombophilia status and women are randomly assigned to ‘standard high risk care’ or ‘standard high risk care’ plus enoxaparin 40 mg from recruitment until 36^+0^ weeks or delivery, whichever occurs sooner. Standard high risk care includes the use of aspirin 100 mg daily and calcium 1000–1500 mg daily (unless only had previous SGA with no preeclampsia).

The primary outcome is preeclampsia and/or SGA <5^th^ customised birthweight centile. Analysis will be by intention to treat.

**Discussion:**

The EPPI trial has more focussed and clinically relevant inclusion criteria than other randomised trials with a more restricted composite primary outcome. The inclusion of standard use of aspirin (and calcium) for all participants will help to ensure that any differences observed in outcome are likely to be related to enoxaparin use. These data will make a significant contribution to future meta-analyses and systematic reviews on the use of LMWH for the prevention of placental mediated conditions.

**Trial registration:**

ACTRN12609000699268 Australian New Zealand Clinical Trials Registry. Date registered 13/Aug/2009 (prospective registration).

## Background

Preeclampsia and intrauterine fetal growth restriction (IUGR) are two of the most common causes of maternal and perinatal morbidity and mortality. Preeclampsia complicates approximately 3–5% of pregnancies and remains one of the most common causes of direct maternal death in the developed world [1]. IUGR is more difficult to define and measure but approximately 10% of all infants will be born small for gestational (SGA) defined as birthweight < 10^th^ customised birthweight centile and at least two thirds of these have evidence of abnormal uterine and umbilical Doppler waveforms if diagnosed prior to birth suggesting significant utero-placental disease and fetal growth restriction [2]. Infants who are born growth restricted with or without maternal preeclampsia are at increased risk of morbidity and mortality during the perinatal period [3–5], and this risk continues into childhood and adult life with higher rates of neurosensory disability, cognitive impairment, short stature, hypertension, diabetes and long term cardiovascular disease [6–11]. Women with preeclampsia and/or IUGR fetuses are more likely to require preterm delivery, with over one third of women with preeclampsia and 15% of SGA infants delivering <37 weeks [12]. Iatrogenic preterm birth often results in operative delivery and therefore has inherent risks to the mother and results in the significant additional risks of prematurity for an already compromised infant [3, 13–15].

There are a wide variety of identified risk factors for preeclampsia and/or IUGR but few contribute significantly to risk prediction models which at best remain modest [16, 17]. Until relatively recently it has been suggested that inherited thrombophilias are associated with preeclampsia and IUGR, however, more recent evidence from prospective cohort studies suggests this association, if present, is only weak [18]. Past obstetric history is the most commonly used method for risk assessment in current clinical practice. Women who have had previous preeclampsia and/or IUGR are at significant risk of recurrence especially when the disease occurred early in the previous pregnancy with rates ranging from 15 to 47% depending on the severity of previous disease [19–22].

Both conditions are considered placental diseases and there are likely synergies in pathological mechanisms which may present as a maternal syndrome (preeclampsia only), a fetal syndrome (IUGR only) or a combined clinical syndrome (preeclampsia and IUGR) depending on fetal and maternal responses to the pathological process. The synergies in the pathological mechanisms have led many investigators to research common therapeutic and preventative strategies for both diseases. Aspirin and calcium have been trialled in a large number of randomised studies in a variety of populations and although effect sizes are modest both significantly reduce the incidence of preeclampsia [23], and aspirin also decreases the incidence of SGA [24]. They should be considered as standard practice in women at high risk of these conditions [25].

Heparin and low molecular weight heparin (LMWH) have also been proposed as potential preventative therapies for a number of placental mediated pregnancy complications including preeclampsia and IUGR. Their effect may relate to their anticoagulant effect although it is also likely that additional effects on trophoblast development may be more significant [26–28]. Initial interest in the use of heparin for the prevention of placental mediated complications centred on the treatment of recurrent miscarriage associated with anti-phospholipid syndrome (APS). Early studies demonstrated significant benefit of unfractionated heparin with aspirin when compared to aspirin alone [29, 30]. This led many clinicians to routinely treat these women with LMWH for all pregnancy complications associated with APS and this practice has continued despite subsequent studies failing to demonstrate the same improvements in pregnancy outcomes with LMWH and aspirin [31, 32].

Some clinicians extended their use of heparin and LMWH for the prevention of preeclampsia and IUGR to women regarded at high risk of these complications for other reasons, such as those with renal disease [33], women with ACE DD polymorphism [34] and women with inherited thrombophilia [35, 36]. These small observational and non-placebo controlled trials suggested significant benefits associated with heparin and LMWH.

Subsequently a number of randomised controlled trials have been reported. Initial trials focussed specifically on populations with or without thrombophilia, believing that the risk of these placental diseases may be significantly different between the groups and may respond differently to intervention with heparin or LMWH. In 2009, Rey et al. reported the outcomes of a randomised trial of LMWH in women with a past history of placental mediated problems (including preeclampsia and IUGR) and no thrombophilia. This trial demonstrated a large reduction in the primary composite outcome (severe preeclampsia, birthweight <5th centile, major abruption or fetal death after 20 weeks) 5.5 vs 23.6% adjOR 0.15, 95% CI 0.03–0.70 [37]. However the study was halted after just over one third of the planned participants had been recruited (results of 110 participants analysed of a planned sample size of 276 women). The FRUIT-RCT reported similar promising outcomes associated with LMWH use for women with inherited thrombophilia, demonstrating a significant reduction in the recurrence of hypertensive disease (preeclampsia, HELLP syndrome and/or eclampsia) <34 weeks gestation, 8.7 vs 0% risk difference 8.7, 95% CI 1.9–15.5%) [38]. This study also did not complete recruitment of initial planned sample size (139 of 262).

Subsequent published trials including the ‘Heparin in pregnant women with adverse pregnancy outcome to improve rate of successful pregnancy’ (HAPPY) Study [39], the ‘Prevention of maternal and perinatal complications by enoxaparin in women with previous severe preeclampsia’ (HEPEPE) Study [40] and the ‘Thrombophilia in Pregnancy Prophylaxis Study’ (TIPPS Study) [41] have failed to demonstrate any improvement in outcome with LMWH.

All of these trials have had prolonged recruitment phases (up to 12 years [41]) and have been difficult to recruit to. Several trials have stopped early due to recruitment difficulties and for perceived overwhelming effect [37] or futility after interim data analysis [39]. Of note, these previous randomised controlled trials have had broad inclusion criteria and diverse composite outcome measures.

The EPPI trial aims to be more precise, and clinically relevant, with its inclusion criteria and primary outcome measures specific to women at high risk of preeclampsia and/or IUGR. Account will be made of each participant’s thrombophilia status but this will not define the study population. Standard high risk care will include the use of aspirin and, where appropriate, calcium for all women. This is the first trial in this setting to also include serial assessment of placental and angiogenic growth factors.

## Methods/design

### Aim

To assess the effectiveness of LMWH, enoxaparin 40 mg daily, for the prevention of recurrence of preeclampsia and IUGR regardless of thrombophilia status and in addition to standard high risk antenatal care (including the use of aspirin and, where appropriate calcium).

### Study design

A multicentre open label randomised controlled trial.

### Study setting

The trial will recruit women from high risk clinic settings in New Zealand at National Women’s Health, Auckland City Hospital; in Australia at the Royal Women’s Hospital, Melbourne, the Mercy Hospital for Women, Melbourne and the Sunshine Hospital, Melbourne; and in the Netherlands at the Academic Medical Centre, Amsterdam.

### Inclusion criteria

Women are eligible for the trial if they are >6^+0^ and <16^+0^ weeks gestation with fetal viability and a singleton pregnancy confirmed on ultrasound scan and at risk of preeclampsia and/or IUGR based on their past obstetric history. This is defined by (1) previous preeclampsia delivered <36^+0^ weeks in their last on-going pregnancy reaching >12 weeks, (2) previous SGA < 10^th^ customised birthweight centile delivered <36^+0^ weeks in their last ongoing pregnancy reaching >12 weeks with no major fetal anomaly or, (3) previous SGA ≤ 3^rd^ customised birthweight centile delivered at any gestation in their last on-going pregnancy reaching >12 weeks with no major fetal anomaly.

### Exclusion criteria

Women are not eligible for the trial if they have (1) any contraindication to LMWH use, (2) a requirement for LMWH use such as previous thrombosis, APS, (3) previous successful pregnancy with LMWH treatment, (4) multiple pregnancy, (5) known pre-existing type 1 or 2 diabetes or renal disease (with serum creatinine >150), (6) thrombocytopenia (platelet count <80 × 10^9^/L) prior to randomisation or (7) a known major fetal anomaly/chromosomal abnormality.

### Trial entry and informed consent

All eligible women will be invited to participate in the study. Trial information will be provided verbally and by a written information sheet by clinicians caring for women and research midwives. Eligible women will be encouraged to take time to consider involvement in the study and to discuss participation with their partners and/or family prior to providing written consent. For women who decline to participate in the trial, antenatal care relevant to their risk factors will be offered, the use of LMWH will not be offered as part of standard care. All trial participants will be free to withdraw from the study at any time if they so wish, appropriate on-going antenatal care will be arranged according to clinical risk.

### Randomisation

A computer generated randomisation programme will be used with stratification for recruiting site and inherited thrombophilia status to ensure equal distribution across study groups. Women who have been tested prior to trial involvement will be assigned to (i) positive thrombophilia or (ii) negative thrombophilia. For women not tested or partially tested (with negative result), samples will be taken before any use of LMWH and tested for antithrombin deficiency, protein C deficiency, protein S deficiency, factor V Leiden, and the prothrombin gene mutation. Results will not be revealed to participant, clinicians or investigators until the study is completed. These women will be assigned to (iii) unknown thrombophilia status. Randomisation will be in blocks of five.

All participants will be assigned a sequential study identifying number (ID) according to thrombophilia status. At the lead recruiting site (National Women’s Health, Auckland City Hospital) randomisation will occur by telephone to the hospital pharmacy clinical trials service and study group allocation made by study ID. In all other sites sequential sealed opaque envelopes for each study ID will be opened to reveal study group.

### Study groups

Women will be assigned to one of two groups; Group one will receive ‘standard high risk care’ and Group two will receive ‘standard high risk care’ and enoxaparin 40 mg sc (Clexane®, Sanofi-Aventis) [42] daily from recruitment (at gestational age >6^+0^ and <16^+0^ weeks) until 36^+0^ weeks or delivery, whichever occurs sooner.

Standard high risk care is defined as care co-ordinated by a high risk antenatal clinic service, aspirin 100 mg daily until 36^+0^ weeks and calcium 1000–1500 mg daily until 36^+0^ weeks (unless only had previous SGA with no preeclampsia as eligibility criteria). This is an open-label randomised study and all participants, clinicians and investigators will be aware of study group assignment.

### Obstetric care and trial procedure (Fig. 1)

**Fig. 1 Fig1:**
[figure not shown]
Individual participant trial schedule

All women will have serum samples taken at recruitment, 20 and 30 weeks gestation. Samples will be centrifuged and stored in −80 °C freezer for later assessment of placental and angiogenic growth factors (Table 1). At the time of fetal anatomy scan, standard fetal growth parameters [43, 44] and uterine and umbilical arterial Doppler waveforms [45] will be recorded. These ultrasound measurements will be repeated at 24 weeks’ gestation. Data from any additional antenatal ultrasound scans will also be collected.

**Table 1 Tab1:** EPPI trial key secondary study outcomes

Combined	Preeclampsia and/or SGA <10th centile Preeclampsia and/or SGA <10th centile delivered <35^+6^ weeks Preeclampsia and/or SGA <10th centile delivered <33^+6^ weeks Preeclampsia and SGA <10^th^ centile delivered at any gestation
Maternal	Preeclampsia Severe preeclampsia Placental abruption Caesarean section delivery Antepartum haemorrhage Postpartum haemorrhage <500mls and <1000mls
Infant	SGA <10^th^ centile SGA <5^th^ centile SGA <3^rd^ centile Unexplained intrauterine fetal death Stillbirth Gestational age at delivery Mean birthweight Mean birthweight centile Neonatal Intensive Care Unit admission Neonatal death
Uteroplacental	Abnormal uterine artery Doppler waveform at 20 or 24 weeks Abnormal umbilical artery Doppler waveform at 20 or 24 weeks
Placental & angiogenic growth factors	soluble fms-like tyrosine kinase-1 (sFlt-1) soluble endoglin (soluble Eng) Endothelin-1 (ET-1) Placental growth factor (PLGF) soluble vascular cell adhesion molecule 1 (VCAM1)

*SGA* small for gestational age, all SGA measured by customised birthweight centile [46]

For women receiving LMWH, an educational session regarding injection technique will be provided by a research midwife prior to treatment commencement. LMWH injections will be re-supplied on a monthly basis from hospital pharmacies. Treatment will continue until 36^+0^ weeks but additional safety indications to stop treatment sooner include; need for delivery prior to 36^+0^ weeks (stop once decision made for delivery or 12 h prior to induction of labour or elective caesarean section, whichever is later), episode of threatened preterm labour (treatment can be recommenced if symptoms settle), clinical evidence of placental abruption or thrombocytopenia with platelet count <80 × 10^9^/L.

Antenatal, intra-partum and postnatal care will be provided by the local obstetric team caring for each woman. Pregnancy, labour, postnatal and neonatal data will be collected by research staff from maternal and infant clinical records up to the time of hospital discharge.

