### Study outcomes

The primary outcome is the incidence of preeclampsia and/or small for gestational age (SGA) <5^th^ customised birthweight centile [46]. Preeclampsia will be defined as new onset hypertension (systolic BP ≥140 mmHg and/or diastolic BP ≥90 mmHg) arising after 20 weeks gestation with evidence of significant proteinuria (dipstick proteinuria (≥1+) subsequently confirmed by spot urine protein/creatinine ratio ≥ 30 mg/mmol and/or 24 h urine protein excretion >0.3 g) or any multi-system complication including haematological, liver, renal and neurological involvement [47]. IUGR is difficult to define and measure and so SGA defined by customised birthweight centiles will be used as the most reproducible surrogate. Customised centiles adjusting for infant sex, gestation at delivery and maternal variables—parity, ethnicity, height and weight will be used [46]. The key secondary study outcomes are shown in Table 1.

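### Table 1 prints the postpartum haemorrhage thresholds with the inequality reversed; separately, two preterm cut-offs in the same table need confirming

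*Protocol article*

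**What the plan says.** The Study outcomes section gives the primary outcome in full and then refers the reader on: "The key secondary study outcomes are shown in Table 1". For the secondary outcomes, Table 1 is therefore the definition that the article gives.

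In the maternal row of Table 1 the bleeding-related entries are "Placental abruption Caesarean section delivery Antepartum haemorrhage" (the first and third of these three), followed by "Postpartum haemorrhage <500mls and <1000mls". No other section defines postpartum haemorrhage.

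The combined row of the same table contains two outcomes restricted by gestation at delivery: "Preeclampsia and/or SGA <10th centile delivered <35^+6^ weeks" and "Preeclampsia and/or SGA <10th centile delivered <33^+6^ weeks". The Inclusion criteria write the corresponding preterm limit for the previous pregnancy in a different form: "previous preeclampsia delivered <36^+0^ weeks in their last on-going pregnancy reaching >12 weeks". The Study groups section also uses 36+0 weeks, as the planned end of enoxaparin, aspirin and calcium.

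**The concern.** Postpartum haemorrhage means excess blood loss, so the event has to lie above a threshold. Table 1 puts it below. The trial adds an anticoagulant to aspirin in one arm, and this is the only postpartum bleeding outcome in the table. If the printed definition were carried into a data dictionary or analysis program, more bleeding on enoxaparin would be tabulated as a lower event rate. If it were noticed only after the open-label data had been seen, a plain erratum could look like a change of outcome.

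The preterm cut-offs raise a smaller and separate question. A strict inequality at 35+6 leaves out deliveries on that day, whereas a strict inequality at 36+0 keeps them. A woman whose previous preeclampsia was delivered at 35+6 qualifies for the trial, but a recurrence delivered on the same day of gestation would not count in the matching secondary outcome.

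**Working it through.** The article states no figure that depends on these signs, so there is none to reproduce. The check has three parts.

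**1. Direction of the haemorrhage outcome.** Input: the two thresholds in the maternal row of Table 1.

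| Blood loss | Event as printed, 500 mL | Event as printed, 1000 mL | Event at or above 500 mL | Event at or above 1000 mL |
|---|---|---|---|---|
| 300 mL | yes | yes | no | no |
| 700 mL | no | yes | yes | no |
| 1500 mL | no | no | yes | yes |

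As printed, the 500 mL category lies inside the 1000 mL category. A severity grading needs the reverse, with the larger loss nested inside the smaller.

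A faulty text conversion is an unlikely explanation. Signs for greater than, and for greater than or equal to, appear correctly in the Inclusion criteria (gestation above 6+0 weeks) and in Study outcomes (systolic pressure at or above 140 mmHg, 24 h protein above 0.3 g).

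**2. Effect of literal use.** Let p be the true proportion losing at least 500 mL. The printed outcome then has proportion 1 − p, so:

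- risk difference as printed = (1 − p_enox) − (1 − p_ctrl) = −(p_enox − p_ctrl)
- risk ratio as printed = (1 − p_enox) / (1 − p_ctrl)

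The protocol gives no haemorrhage rates. The rates below are assumptions, spread over a range:

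| Assumed control, enoxaparin | True difference | True ratio | Printed difference | Printed ratio |
|---|---|---|---|---|
| 10%, 15% | +5 points | 0.15/0.10 = 1.50 | −5 points | 0.85/0.90 = 0.944 |
| 20%, 30% | +10 points | 0.30/0.20 = 1.50 | −10 points | 0.70/0.80 = 0.875 |
| 30%, 40% | +10 points | 0.40/0.30 = 1.33 | −10 points | 0.60/0.70 = 0.857 |

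The change of sign follows from the algebra and does not depend on the assumed rates. Only the sizes do.

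**3. Preterm cut-offs.** Convert gestation to days as 7 × weeks + days. The last day that a strict inequality counts is the cut-off minus one.

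- Below 35+6: 7 × 35 + 6 = 251, last day counted 250, which is 35+5.
- Below 36+0: 7 × 36 = 252, last day counted 251, which is 35+6.
- Below 33+6: 7 × 33 + 6 = 237, last day counted 236, which is 33+5.
- Below 34+0, for comparison only: 7 × 34 = 238, last day counted 237, which is 33+6.

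The first gap is one day against a limit that the protocol itself uses. The second gap is one day only if 34+0 was meant. The protocol uses no 34-week limit in its own definitions; 34 weeks occurs only in the Background, for another trial's outcome.

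**The case against.** The best defence is that the haemorrhage line exposes itself as a slip. The word haemorrhage next to a less-than sign makes no sense, and an analyst would probably notice. The article condenses a fuller protocol, and nothing shown indicates that the case report form or data dictionary repeats the error. Safety oversight does not rest on this line either, because the data monitoring committee reviews serious adverse events and may advise stopping for an excess on heparin. All of this stands, and it limits the likely harm. It does not make the printed definition right. The article states the outcome wrongly rather than leaving it to another document.

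On the preterm cut-offs the defence is stronger. Both are clear, computable and the same in the two arms. The eligibility limit describes the previous pregnancy and the outcome the current one, and nothing says that they must match. One eligibility route, SGA at or below the 3rd centile, has no gestational limit at all. That the one-day gap is unintended is plausible, but it is an inference.

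A reader might go further in three ways that the protocol does not support:

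- That the main bleeding outcome is reversed. The protocol names no such outcome. Postpartum haemorrhage is one of six maternal entries in Table 1, beside antepartum haemorrhage and placental abruption, and the entries are not ranked.
- That the preterm cut-offs add to the reversed bleeding direction. They have no bearing on it.
- That the preterm cut-offs are wrong. For 35+6 there is an inconsistency of notation to be settled. For 33+6 the trial's own definitions offer nothing to compare it with.

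**Conclusion.** The haemorrhage thresholds in Table 1 are reversed as printed, and nothing in the article corrects them. Literal use would reverse the sign of any group difference in a safety-relevant secondary outcome of an anticoagulant trial. The percentages above only illustrate this, since they rest on assumed rates, and the reversal occurs only if the text is applied as it stands. The correction should be made because it is specific and nearly free.

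The preterm cut-offs are a minor point of confirmation. Each leaves out deliveries on one named day, and the first differs by one day from the eligibility limit. No bias towards either arm is shown.

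The primary outcome, sample size, power and interim analysis are untouched by either point.

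**What to change.** In Table 1, restate postpartum haemorrhage as blood loss at or above 500 mL and at or above 1000 mL. Check that the data dictionary and any analysis program use the same direction. This is an erratum of one line, with no effect on data collection or sample size.

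Separately, ask the investigators whether the combined outcomes were meant to include deliveries on 35+6 and on 33+6. If so, write them as at or below 35+6 (the same as below 36+0) and at or below 33+6. If the printed cut-offs were intended, keep them and say so. Because a change here would alter two secondary outcome definitions unless a slip is confirmed, the answer should be recorded with its date, and preferably settled before outcome data are compared by group. The cost is one query and, if needed, two edits to the table.
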